## Abstract

**Background:**

Striae gravidarum (stretch marks) are considered the most common connective tissue/skin change in pregnancy. Though not a health issue they can affect women in different ways, for example, cause stress or be an aesthetic or cosmetic concern. Many women use one or more of the commercially available products to try and prevent their development during pregnancy despite the fact that that there is a lack of high-quality evidence to support their use. There is a dearth of studies on the prevention of striae gravidarum and large, robust trials are lacking. Until such time as more products are investigated, much of the knowledge remains anecdotal. This pilot study will evaluate the feasibility of conducting a study to evaluate the effectiveness of a commercially available moisturising oil compared to no treatment for the prevention and reduction in severity of striae gravidarum.

**Methods:**

The definitive study will be a randomised controlled trial to evaluate the effectiveness of a moisturising oil (commercially available moisturising oil) compared to no treatment for the prevention and reduction in severity of striae gravidarum. This protocol is for a pilot randomised trial to evaluate the feasibility of conducting such a study. The pilot study will be a two-arm, unblinded, pragmatic parallel randomised trial with a 1:1 randomisation ratio between control and intervention groups. Women in the intervention group will be asked to apply a moisturising oil to their abdomen during pregnancy, while women in the control group will not use any treatment. It is proposed to recruit 20 primigravida, who are 12–16 weeks pregnant from an Irish Maternity Hospital, in each arm to assess the feasibility of running such a trial.

**Discussion:**

This pilot trial will evaluate the feasibility of conducting the main study to evaluate the effectiveness of a moisturising oil (commercially available moisturising oil) compared to no treatment for the prevention and reduction in severity of striae gravidarum. It will potentially initiate the generation of high-quality evidence to guide women in their choice of anti-stretch mark product.

**Trial registration:**

ISRCTN Registry, ISRCTN76992326. Registered on 14 July 2017.

**Electronic supplementary material:**

The online version of this article (10.1186/s13063-018-2898-7) contains supplementary material, which is available to authorized users.

## Background

Striae gravidarum or stretch marks occurring in pregnancy are considered the most common connective tissue change in pregnancy [1]. They affect all racial groups [2], with reported rates of occurrence usually in the range of 52–90% in women of different ethnicities [3–7]. Striae gravidarum are common during the first pregnancy [8] and usually present during the third trimester [9]. Striae start as ‘reddish slightly depressed streaks’ [9] (p. 111) and fade gradually [8] to leave pale wrinkled lines [10], which are permanent skin changes [11, 12] . These benign skin changes [4] occur commonly on the abdomen but are also seen on the breasts and thighs [8, 9, 13] and the hips and buttocks [14].

The exact cause of striae gravidarum remains unclear [5] but is considered to be related to the effects of stress on the tissue or stretching of the skin and hormonal effects [1, 15].

Risk factors associated with the development of striae gravidarum have been identified [4, 6], albeit inconsistently [16]. While some risk factors are modifiable, others are not [16]. Two of the commonly identified risk factors are higher weight gains in pregnancy [4, 5, 7] and higher birth weight babies [2, 4, 6, 13, 17]. Other risk factors include a family history [6, 7, 16, 18–20], a personal history of striae [18] and young maternal age [5, 13, 17, 19–21].

Though not a health issue [8, 14, 17], striae gravidarum have concerned women since early times [8] and continue to do so. They have caused anxiety or psychological/emotional distress to some women [8, 20, 22], while for others they are an aesthetic or cosmetic concern [4–6, 14, 18–20] and can impact negatively on a woman’s self-esteem and body image [14]. Consequently, many women during pregnancy have tried to prevent or treat striae gravidarum over the years and often at great expense [8] and indeed continue to do so [23].

### Prevention and treatment of striae gravidarum

There are many products available for women to choose during pregnancy purporting to prevent [24] or treat [14] striae gravidarum [5, 17, 21, 23, 25]. In one recent large survey involving 753 pregnant women [23], most respondents (78.2%, *n* = 589) indicated that they used a product to prevent or reduce the development of stretch marks during the current pregnancy and over one-third (36.5%, *n* = 210) had used two or more products.

The highest-quality evidence available to date on the prevention of striae gravidarum is from a recent Cochrane Review [26] which evaluated the effects of topical preparations on the prevention of stretch marks in pregnancy. Six trials with 800 women were included in the review which found that there was no statistically significant average difference in the development of striae gravidarum in women who received topical preparations with active ingredients compared to women who received a placebo or no treatment (average risk ratio [RR] 0.74; 95% confidence interval [CI] 0.53–1.03; five trials, 474 women; random-effects model, Tau^2^ = 0.09, I^2^ = 65%). There was also no statistically significant average mean difference in the severity of striae gravidarum (standardised mean difference [SMD] – 0.31; 95% CI – 1.06–0.44; two trials, 255 women; Tau^2^ = 0.26, I^2^ = 87%).

Similarly, there was no statistically significant difference between women who received topical preparations with active ingredients compared to women who received other topical preparations with active ingredients in the development of striae gravidarum (average RR 0.51; 95% CI 0.16–1.60; two trials, 305 women; Tau^2^ = 0.53, I^2^ = 74%) or in the severity of striae gravidarum (mean difference [MD] – 0.20; 95% CI – 0.53–0.13; one trial, 206 women; heterogeneity not applicable). The authors concluded that they found no high-quality evidence to support the use of any of the topical preparations evaluated in the review [26].

### Why a trial is needed?

The prevention of striae is important to women [27] and women often ask how they can be prevented during pregnancy [5, 16]. There is a dearth of studies on their prevention and large, robust trials are lacking [26, 28]. This protocol is for a pilot randomised trial to evaluate the feasibility of conducting a larger trial and will compare a moisturising oil versus no treatment for the prevention and reduction in the severity of striae gravidarum. The null hypothesis for the future definitive trial is that there will be no difference in the proportion of participants who develop striae gravidarum or in the severity of the striae between the group who apply the moisturising oil and the group who do not apply any product.

All aspects of the pilot protocol presented here are informed by the 2013 Standard Protocol Items as per Recommendations for Interventional Trials (SPIRIT) statement [29], which seeks to ensure high-quality trial protocols.

## Methods

The definitive study will be a randomised controlled trial to evaluate the effectiveness of a moisturising oil (commercially available moisturising oil) compared to no treatment for the prevention and reduction in severity of striae gravidarum. This protocol is for a pilot randomised trial to evaluate the feasibility of conducting such a study. The study will follow the SPIRIT guidelines for the design and conduct of a trial (Fig. 1; Additional file 1). The pilot study will be a two-arm, unblinded, pragmatic parallel randomised trial with a 1:1 randomisation ratio between control and intervention groups, comparing the effectiveness of a moisturising oil (commercially available moisturising oil) compared to no treatment for the prevention and reduction in severity of striae gravidarum.

**Fig. 1 Fig1:**
[figure not shown]
Standard Protocol Items: Recommendations for Interventional Trials (SPIRIT) schedule of enrolment, interventions and assessments for the duration of the study

While a randomised trial design is the most effective design for testing the effects of a healthcare intervention [30], a pilot trial enables the testing of the feasibility and acceptability of undertaking a larger trial [31]. It will also contribute to modification of the trial protocol for a larger study [31].

### Objectives of the pilot trial

Measure recruitment, enrolment, completion, adherence and attrition (withdrawal, drop outs) rates;Evaluate recruitment and randomisation processes;Evaluate the data collection instruments;Collect qualitative data on reasons for refusal to participate; reasons for non-adherence with the intervention and control guidelines and reasons for attrition;Ascertain women’s rating of the tolerability/acceptability and effectiveness of the intervention;Measure the completeness of data collection for outcomes;Evaluate the data analysis methods.

As this is a feasibility study, formal hypothesis testing will not be performed. Suitable descriptive statistics and graphical summaries will be used to summarise participant characteristics. Means and standard deviations will be used for continuous variables; counts and percentages will be used for categorical variables with accompanying 95% CI estimates.

### Participants

#### Eligibility criteria for participants

##### Inclusion criteria

Primigravid women;Singleton pregnancy;12–16 weeks of gestation at time of recruitment;Absence of abdominal striae;Aged ≥ 18 years at recruitment;English-speaking women.

##### Exclusion criteria

Multigravid women (due to risk of having striae from an earlier pregnancy);Women taking corticosteroids for any reason (due to their association with skin striae);Multiple pregnancy (due to increased maternal weight gain and skin stretching);Women with a known hypersensitivity to agents in baby oil (due to risk of allergic reaction);Women with known disorders or illnesses that may be associated with striae, e.g. Marfan syndrome, Cushing syndrome;Women who decline to discontinue other creams or lotions;Women who are unable to give informed consent.

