#### Outcome measures

In order to evaluate the feasibility of conducting a definitive randomised controlled trial to evaluate the effectiveness of a moisturising oil (commercially available moisturising oil) compared to no treatment for the prevention and reduction in severity of striae gravidarum, the outcomes for this pilot study are:Number and proportion of women who are recruited, enrolled, complete the study and adhere to the intervention and control guidelines;Percentage of potentially eligible women who are recruited/enrolled to the study;Challenges with the randomisation process;Number and proportion of women who withdraw, drop out or deviate from the protocol guidelines;Reasons for non-recruitment, non-adherence or attrition;Women’s rating of the tolerability/acceptability and effectiveness of the intervention;Completeness of data collection for outcomes;Challenges with data analysis;Number and proportion of women developing striae gravidarum in the intervention and control groups;Number and proportion of women developing mild, moderate or severe striae gravidarum;Women’s perception of the severity of striae gravidarum (Fig. 1).

In addition to the above outcomes, birth data will also be collected following each birth from the labour ward register on birth gestation and infant weight (Fig. 1) and recorded on the outcomes assessment form.

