#### Recruitment to the trial

Given that most first-time mothers will be eligible for inclusion in the study, an ethics committee-approved study information pack will accompany the booking appointment notification sent to each first-time mother by the clinic administrator. The study pack will include a letter inviting the woman to participate in the study and an information leaflet describing the background, purpose and study details. The information leaflet will provide contact details should potential participants have questions about any aspect of the study. This process ensures participants have time to decide whether they wish to participate and complies with best practice in obtaining consent [37].

The researcher will approach women as they wait for their booking appointment in the clinic while the support of midwives and obstetricians will be sought in identifying potentially eligible women. Thus, at each antenatal booking clinic during the recruitment phase, all primigravid women will be approached by the researcher or a research assistant and given the opportunity to discuss the study details before inviting them to participate in the study. A trial register form will be completed for each woman and each woman screened will be assigned a unique study ID number.

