**Fig. 2 Fig2:**
[figure not shown]
Flow of participants through the trial

Women who agree to participate will be asked to sign three copies of the consent form and these will also be signed by the researcher. One copy will be returned to the woman, one will be put in the woman’s hospital records and the third will be kept for the research records. Women who are eligible and who decline to participate will be asked for their consent to disclose their reasons for non-participation. Further, women who subsequently decide to withdraw from the study will be asked to contact the researcher as outlined on the participant information leaflet**.** Women will then be asked by the researcher over the phone to give their consent to: (1) retention of data collected before their withdrawal from the study; or (2) retention of data collected before their withdrawal from the study and the inclusion of data collected routinely; or (3) that they wish to withdraw completely.

When written consent is obtained as outlined, the researcher will select the next sequentially numbered opaque envelope with the woman’s allocation. The researcher will then record the woman’s name and the envelope number in the woman’s trial register form in the presence of another colleague; they will both then sign the unopened envelope. Following this, the researcher will open the envelope revealing the group allocation and study ID, both of which will be recorded in the trial register form as above.

Women will complete a demographic and baseline characteristics’ data form as part of the case report form (CRF), which seeks information on name, date of birth, medical history, drug use, smoking status, maternal body mass index (BMI) at enrolment (BMI will also be assessed at 38–41 weeks of gestation at time of outcome assessment) and family history of first-degree relative developing striae in pregnancy.

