### Criteria for proceeding to the main trial

The decision to proceed to the main trial will be made by the Trial Steering Committee based on the following criteria:≥ 40% of eligible women can be recruited;≥ 70% of women adhere to the intervention and control guidelines;<  20% of women lost to follow-up.

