### Statistical analysis

Data will be entered into a secure database using the Statistical Packages for the Social Sciences (SPSS) version 21 [39] as collected. Data will be coded and cleaned. As this is a feasibility study, formal hypothesis testing will not be performed. Suitable descriptive statistics and graphical summaries will be used to summarise participant characteristics. Means and standard deviations will be used for continuous variables; counts and percentages will be used for categorical variables with accompanying 95% CI estimates.

In addition, numbers and percentages of women recruited, eligible, randomised, enrolled and who completed the trial will be outlined in a CONSORT flow chart.

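### Women who will not stop their own creams are classed as ineligible, so this form of refusal drops out of the denominator of the 40% recruitment criterion

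*Protocol article*

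**What the plan says.** - **Exclusion criteria (protocol article).** One listed exclusion is "Women who decline to discontinue other creams or lotions". The Experimental intervention and Control intervention sections ask women in both arms to use no other skin product on the abdomen.
- **Criteria for proceeding to the main trial.** The recruitment criterion is that at least "40% of eligible women can be recruited". The Trial Steering Committee decides on this and two other criteria.
- **Outcome measures.** The matching outcome has another denominator: "Percentage of potentially eligible women who are recruited/enrolled to the study". The article does not define potentially eligible. The same list includes "Reasons for non-recruitment, non-adherence or attrition".
- **Enrolment to the trial (text after Fig. 2).** "Women who are eligible and who decline to participate will be asked for their consent to disclose their reasons for non-participation".
- **Recruitment to the trial.** "A trial register form will be completed for each woman and each woman screened will be assigned a unique study ID number".
- **Statistical analysis.** The "numbers and percentages of women recruited, eligible, randomised, enrolled and who completed the trial will be outlined in a CONSORT flow chart".
- **Prevention and treatment of striae gravidarum.** In a survey of 753 pregnant women, 78.2% (589) "indicated that they used a product to prevent or reduce the development of stretch marks during the current pregnancy".

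**The concern.** Several of the other exclusions carry a stated medical reason, such as corticosteroid use, multiple pregnancy or hypersensitivity. This one turns on willingness. A woman who meets every other criterion but will not give up her product is declining the trial's conditions. The sample size section itself separates women who will refuse from women who will not be eligible, and the exclusion list moves one kind of refusal into the second group.

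Two things follow if the sections are applied as written. The 40% criterion is calculated without these women, so it cannot register this kind of refusal however common it is. And the procedure for asking reasons does not reach them, although collecting reasons for refusal is one of the pilot's objectives. Whether women will forgo their own products bears directly on the feasibility of a trial with a no-treatment control, and the recruitment criterion is one of three that decide progression.

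**Working it through.** **The plan's own figures.** The 40% threshold is a chosen cut-off with no derivation, so there is nothing to reproduce. The survey figure agrees: 589/753 = 78.2%.

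**Inputs.**
- Reported recruitment rate, r = recruited / eligible. The threshold is r = 40% (Criteria for proceeding to the main trial).
- w = share of otherwise-eligible women who decline to stop other products. The documents do not give it, so the values below are assumptions.

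**Formula.** Let N women meet every criterion except possibly this one. Then wN are classed as ineligible and (1 − w)N as eligible. None of the wN is recruited under either coding, so the number recruited is r(1 − w)N. Uptake among all otherwise-eligible women is

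u = r(1 − w), or equivalently r = u/(1 − w).

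For any w > 0 the reported rate is therefore higher than u, by a factor of 1/(1 − w).

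**Example in counts.** Take N = 100 and w = 30%. Then 30 are excluded, 70 are eligible, and 28 are recruited if r = 40%. The criterion reads 28/70 = 40%. Uptake is 28/100 = 28%.

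**Over a range of assumed w, with a reported 40%:**

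| w (assumed) | u = 0.40 × (1 − w) | factor 1/(1 − w) |
|---|---|---|
| 10% | 36% | 1.11 |
| 30% | 28% | 1.43 |
| 50% | 20% | 2.00 |

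**In reverse.** An uptake of 25% shows as 0.25/0.60 = 41.7% at w = 40% and passes. It first reaches the threshold at w = 1 − 0.25/0.40 = 37.5%.

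**The two denominators.** The progression criterion uses eligible women; the recruitment outcome uses potentially eligible women. If the second term includes the wN women, the outcome estimates u while the criterion uses r. The pilot could then report 28% for one and 40% for the other from the same 28 recruits.

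**The case against.** The case on the other side has five parts.

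- **The group can be counted.** Every screened woman gets a register form and an ID, the flow chart shows numbers eligible, and reasons for non-recruitment are an outcome not limited to eligible women. The Data monitoring section also has the researcher follow reasons for non-recruitment of potentially eligible women. And for this group the ground for exclusion is itself a reason. This stands: a reader might infer that these women vanish from the record, and the documents do not support that. But none of these provisions changes the denominator of the rule that decides progression.
- **Some of this reluctance is still counted.** Discontinuing most naturally describes current users. A woman who uses nothing yet but will not risk a no-product control is eligible, declines, and is asked why. This stands and limits how large w can be; it does not make w zero.
- **The rate may carry over.** If the main trial keeps the same exclusion, recruited over eligible is the matching rate, provided it is used with the eligible share seen at screening. So it does not follow automatically that main-trial recruitment would be overestimated. That happens if the 40% is applied to a wider pool, which is a real risk because the Recruitment section expects most first-time mothers to be eligible. Assuming, for illustration only, that all of the roughly 80 monthly bookings are otherwise eligible, 40% gives 80 × 0.40 = 32 recruits a month; with w = 40% it gives 80 × 0.60 × 0.40 = 19.2.
- **Heavy screening losses would show.** They would appear as slow accrual, which is monitored and overseen by the steering committee. True, but the stated recruitment criterion would still read as met.
- **Coding is detail for a fuller document.** An article need not describe the screening log. Here, however, the exclusion and the denominator are both stated, and the problem comes from reading them together.

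A reader might also infer that unwillingness to stop a product is the main reason for refusal, or that the 78.2% estimates w. Neither is supported. No section ranks reasons for refusal. The survey figure is use at some time in the current pregnancy, not use at 12–16 weeks and not unwillingness to stop.

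**Conclusion.** The point holds in a limited form. As written, a refusal of a condition that applies to both arms is classed as ineligibility. It leaves the denominator of the 40% criterion and falls outside the stated procedure for asking reasons. The recruitment outcome uses a different, undefined denominator.

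The direction is certain for any w above zero; the size is not known. The 36%, 28% and 20% figures illustrate assumed values of w and measure nothing. The high product use in the survey makes a non-trivial w plausible, and that is as far as it goes. The conclusion rests on reading the exclusion list and the progression criterion literally, with eligible meaning that no exclusion applies.

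Because the criterion bears on whether the main trial goes ahead and the correction is cheap, it should be made.

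**What to change.** 1. Continue not to enrol these women. On the trial register form and in the flow chart, code them separately as otherwise eligible, declined to stop other products.
2. Extend the request for reasons in Enrolment to the trial to this group, with the same consent.
3. Define one denominator that includes them, and use it both for the recruitment outcome and for the 40% criterion. At the least, give the Trial Steering Committee the criterion with and without them.

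The cost is one register code and one sentence in the protocol. The reported recruitment rate becomes less favourable, and the 40% threshold becomes harder to meet. The Trial status section says that no participant had yet been enrolled, so no enrolled woman's data are affected; women already screened would need the same code.
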